#### Traditional self-training

The GRASP (Graded Repetitive Arm Supplementary Program) [8], which is a self-directed arm and hand exercise program developed for individuals with stroke with upper extremity impairments, will be used. It is comprised of instruction manuals suited to the functional level of the upper extremity and an equipment kit (such as a towel, a ball and pegs). This self-training intervention has been proved to be more efficient than an educational program for improving the weaker upper extremity post stroke [8] and can be freely downloaded from the Internet (http://neurorehab.med.ubc.ca/grasp/). More so, the GRASP has been implemented in many stroke rehabilitation centers as a cost-effective way to improve the function of the weak upper extremity [22].

### Implementation of the intervention

Individuals will be approached during their first week in rehabilitation and their written consent will be obtained. Following the first assessment, individuals will be randomly allocated to receive self-training either by Rehab-let (experimental group) or GRASP (control group). Concealed allocation will be maintained. A single session will be provided to each participant by an occupational therapist (OT) to teach them how to play the apps (experimental) and perform the exercises (control). Each participant will also receive a booklet with explanations and photographs of the self-training apps/exercises and a log sheet. Participants will be requested to fill in a dailylog regarding their training time. In addition, participants will be asked to indicate whether they have had assistance or someone present during the self-training. Participants will be instructed to play the apps (experimental)/perform the exercises (control) with their weaker upper extremity for a total of 60 minutes a day for 5 days over a 1-month period. The 60 minutes can be divided into 2 or 3 daily sessions. The OT will monitor the participants weekly to assure training is been performed daily, to verify logs are filled in accurately, to adapt the level of the apps/exercises if needed, and to assure that there are no adverse effects. Participants will be given the OT's phone number and will be encouraged to contact him/her during the week, if needed. Participants randomized to the Rehab-let self-training will be taught how to play 4–5 different apps on the tablet, selected together with the OT from a pool of 20 apps. These apps will be available for them in a folder on the iPad’s screen. See Table 2 for a summary of the study’s interventions.

**Table 2 Tab2:** Description of study interventions based on the intervention description and replication (TIDieR) template [38]

Brief name	Rehab-let
Why	Increasing treatment intensity can improve the impaired dexterity of the weaker upper extremity however there is insufficient training time for the weak upper extremity during subacute stroke rehabilitation
What	a. Existing iPad Apps (from the Apple Store (Apple Inc., Cupertino, CA, USA)) using the Rehab-let protocol (experimental), traditional treatment aids such as blocks, pegs and a towel using the GRASP protocol (control)
	b. A printed manual for self-training of hand movements with description and photos of the apps (experimental) or of the exercises (control)
Who provides	Intervention (supervision) and assessments will be performed by occupational therapists who are experts in neurological rehabilitation
How	The intervention will include self-training during inpatient rehabilitation. Face- to-face individual follow-up meetings with the occupational therapists will occur once a week
Where	Intervention will take place in in-patient rehabilitation departments. Participants can self-train either in their room or in a quiet corner in the department
When and how much	Individuals will be requested to self-train 60 minutes a day, 5 times per week for 4 weeks (total of 20 sessions). Four meetings with the occupational therapist will be held during this time as well as pre and post assessment sessions
Tailoring	Different apps from a pool of about 20 apps that facilitate finger and hand movement (experimental) or different exercises from the GRASP protocol (control) will be taught to each participant according to the motor ability of their upper extremity and preference

#### Outcome measures

The primary outcome measure is improved dexterity, which will be assessed by The Nine Hole Peg Test (NHPT) [23]. This test is a valid and reliable test to assess dexterity in individuals with stroke [24] and the time to insert and remove 9 pegs is measured. The following secondary outcome measures will be used; grip and pinch strength [25] will be assessed by the Jamar and pinch dynamometer. The Fugl-Meyer Motor Assessment [26] will assess the motor impairment of the upper extremity. The Action Research Arm Test [27] will assess the functional ability of the upper extremity by grasping and moving objects of different size and weight. The Visual Analogue Scale [28], which quantifies the perceived level of pain intensity on a scale of 0–10 cm, will also be used. Self-training time will be used to assess adherence to the self-training protocol and will be taken from the daily logs. Satisfaction from the self-training program will be determined by a Satisfaction Questionnaire, developed for the study. The questionnaire will query the participant's satisfaction with the self-training intervention and his or her perceived benefit of the intervention to improve upper extremity’s function. Responses will be rated on a scale of 1–5. The System Usability Scale [29] will be filled in by individuals in the Rehab-let group – to assess their subjective usability of the tablet for rehabilitation. Each of the 10 items is rated on a 5-point scale from 1 (disagree totally) to 5 (agree totally), an overall score is calculated ranging from 10 (low usability) to 100 (high usability) points. Demographic and stroke characteristics will also be collected at baseline as well as information regarding prior tablet experience. In addition, independence in basic activities of daily living of this population will be characterized using the Functional Independence Measure [30].

#### Data collection

The clinical measures mentioned above will be administered pre and post the intervention to test the effectiveness of the intervention. See Fig. 1 for study flow.

**Fig. 1 Fig1:**
[figure not shown]
Study flow design

#### Blinding

Assessments pre and post the 4-week self-training intervention will be administered by assessors blinded to the group allocation. See Fig. 1 for study flow.

#### Study samples

A total of forty participants will be recruited for this pilot study: 20 randomized to the Rehab-let self-training protocol (experimental group) and 20 to the GRASP self-directed training (control group). These results will be sufficient to calculate the effect size to use in sample size power calculations for a larger RCT.

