**Discussion:**

The outcomes of this study will inform the design of a fully powered randomized controlled trial to evaluate the effectiveness of Rehab-let. If found to be effective, Rehab-let can be used during subacute rehabilitation to increase treatment intensity and improve dexterity. Potentially, Rehab-let can also be used after discharge and might be ideal for individuals with mild stroke who are often not referred to formal rehabilitation.

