Tablets have been recently used in pilot studies in rehabilitation. The iPad (Apple Inc., Cupertino, CA, USA) was perceived as a helpful tool for enhancing engagement in therapeutic activities and socialization [18] and found to have potential use for hand rehabilitation of individuals with stroke [19]. These preliminary findings support the potential use of tablets for stroke rehabilitation and the need for further research [18]. There are many health-related apps for tablets (e.g., to promote physical activity, monitor salt intake, weight loss); however, commercially available apps for rehabilitation of impaired dexterity are scarce and some of them are not released for public use. For example, Saposnik et al. [20] are currently examining their newly developed Stroke Rehab® game app for home-based rehabilitation poststroke. Countless game apps, which can be downloaded from the App Store (Apple Inc., Cupertino, CA, USA) or Google Market (Google, Mountain View, CA, USA), have been developed for the healthy general population. Despite the fact that they encourage finger and hand movement while playing fun games, only a limited number of apps might be successfully played by individuals with motor impairments due to stroke. Whereas the development of apps specifically for rehabilitation is warranted, it is unknown if existing tablet apps, that are accessible to everyone, can be used by individuals recovering from stroke with a mild to moderate motor upper extremity impairment. More so, due to the tablet's unique characteristics, it is unknown if playing these apps would result in improved dexterity, increased self-training time and higher client satisfaction compared to traditional directed self-training. We therefore propose a pilot randomized controlled trial (RCT) to compare the effectiveness of Rehab-let, a self-training protocol utilizing tablet technology with existing apps, to a traditional self-training program to improve impaired dexterity of individuals with stroke [8]. Individuals during subacute stroke rehabilitation will be targeted first since they receive on-going professional supervision. We hypothesize that using touchscreen tablets with existing, appropriately selected apps (Rehab-let), will result in improved dexterity, increased self-training time and high satisfaction in individuals with stroke as compared to the control group. These preliminary findings will assist with planning a future fully powered RCT.

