### Trial design

A pilot single-blind randomized controlled study with assessments pre and post the intervention. Participants will be randomized by block randomization using an allocation ratio of 1:1 to receive self-training either by Rehab-let using the tablet or by performing traditional activities/exercises. All participants will perform the self-training in addition to the standard rehabilitation care.

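### Twenty patients per arm do not give an effect size precise enough to size the larger RCT, although the article says they will be sufficient for that

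*Protocol article*

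**What the plan says.** Study samples sets the size: "A total of forty participants will be recruited for this pilot study", split 20 and 20. Trial design confirms equal allocation: "Participants will be randomized by block randomization using an allocation ratio of 1:1". The justification follows in one sentence: "These results will be sufficient to calculate the effect size to use in sample size power calculations for a larger RCT". No SD, expected effect, precision target, significance level, power or dropout allowance accompanies it.

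The Background gives the same purpose in softer terms: "These preliminary findings will assist with planning a future fully powered RCT". Data collection goes further and says that the clinical measures are taken before and after training "to test the effectiveness of the intervention".

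The Data analysis plan compares NHPT times by a two-group, two-time-point repeated-measures ANOVA. It names 32.8 seconds as a clinically meaningful change on that test, but does not connect this figure to the size of this trial or the next.

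**The concern.** The sentence in Study samples is a positive claim about what the design can deliver, and it is the sole basis for n = 40. It is therefore not a detail that a condensed article may leave to a fuller document. The claim concerns fitness for a purpose: the observed effect size is to go into the power calculation of the next trial.

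Required sample size varies with the inverse square of the effect size, so error in the effect is magnified in the sample size. If the pilot estimate is too high by chance, the RCT will be underpowered. If it is too low, the RCT will be larger than needed, or the estimate may point the wrong way and give no usable size. The comparator is GRASP, an active programme with the same prescribed training time, so a modest difference between arms is plausible. Imprecision does most damage there.

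**Working it through.** **Inputs from the article.** n = 20 per arm, 1:1 (Study samples, Trial design). The outcome is continuous, NHPT time (Outcome measures). In a 2 × 2 repeated-measures ANOVA the time-by-group interaction is equivalent to a t-test on change scores, here with 20 + 20 - 2 = 38 degrees of freedom.

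**Assumed, because the article gives none of these.** 95% confidence intervals; two-sided 5% significance and 80% power for the later RCT; approximately normal change scores; true standardised effect d from 0.3 to 1.0; all 20 per arm analysed.

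**The plan's own figure.** 20 + 20 = 40 checks. Nothing in the article allows 40 to be derived from a precision or power target.

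**Step 1: precision of d.** SE(d) = √(2/n + d²/(4n)). At d = 0.5, n = 20: √(0.1 + 0.003125) = 0.321, so the half-width is 1.96 × 0.321 = 0.63. It is 0.62 at d = 0 and 0.64 at d = 0.8. The exact noncentral-t interval for an observed 0.5 is -0.13 to 1.13. With 16 analysed per arm the half-width is about 0.70.

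**Step 2: what that interval means for the next trial.** N per arm = 2(1.960 + 0.842)²/d² = 15.7/d². At d = 0.5 this is 62.8, so 63 (64 by the t-based calculation). At the upper limit of 1.13 it is 12.3, so 13. At the lower limit the sign is reversed and no sample size exists.

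**Step 3: how often the next trial is sized wrongly by a factor of two.** Since N is proportional to 1/d², N falls below half the need when observed d > √2 × true d. It exceeds double when observed d < true d/√2, which includes zero and wrong-sign estimates. By hand at true d = 0.5 the cut-offs are 0.707 and 0.354:

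- (0.707 - 0.5)/0.321 = 0.645, upper tail 0.26
- (0.354 - 0.5)/0.321 = -0.455, lower tail 0.32
- total 0.58

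The noncentral-t distribution with continuous N, and the result when N is rounded to whole patients, are:

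| True d | N under half | N over double, or wrong sign | Total, continuous N | Total, whole patients |
|---|---|---|---|---|
| 0.3 | 35% | 39% | 74% | about 74% |
| 0.5 | 27% | 32% | 59% | about 58% |
| 0.8 | 17% | 23% | 40% | about 38% |
| 1.0 | 13% | 18% | 31% | about 27% |

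The choice of sizing formula and rounding rule moves the last two rows by a few points (35% to 40% at 0.8, 25% to 31% at 1.0). Wrong-sign estimates alone are 17% at d = 0.3 and 6% at d = 0.5.

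At true d = 0.5, leaving out the roughly 8% of pilots with an observed d of 0.05 or less, the middle half of pilots would suggest about 30 to 135 per arm, where 64 are needed.

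**Step 4: what 40 patients can estimate.** The limits for the SD are √(38/χ²) on 38 degrees of freedom: √(38/56.90) = 0.82 and √(38/22.88) = 1.29 times the estimate. If the target difference is fixed in seconds, N is proportional to SD², so the error factor in N runs from 0.82² = 0.67 to 1.29² = 1.66. That stays within a factor of two at both 95% limits.

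**The case against.** This is a self-declared pilot. Using its results to plan a larger trial is legitimate, and the article calls its findings preliminary. An effect size can indeed be calculated from 40 patients. All of that is true, but the sentence says that the effect size will suffice for the power calculation, and the figures do not bear that out.

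Four stronger readings are tempting and should not be drawn.

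- **That the next trial would be mis-sized more often than not.** This depends on what counts as mis-sized and on the true effect. On the factor-of-two definition it holds up to about d = 0.6 and fails at 0.8 and above. Counting only trials with true power below 80% (54% of usable pilots at d = 0.5) says little, because any roughly median-unbiased estimate exceeds the truth about half the time.
- **That the article treats the pilot as proof of benefit.** The abstract's Discussion says "If found to be effective, Rehab-let can be used during subacute rehabilitation to increase treatment intensity and improve dexterity", but the sentence before it speaks of a fully powered trial to evaluate effectiveness, so the condition can refer to that later trial. The closing Discussion also calls for a full RCT. The phrase in Data collection is the one clearly out of line.
- **That a chance-low pilot would end the programme.** The article has no go/no-go or futility rule.
- **That no clinical anchor exists.** The 32.8 seconds is stated; it is simply not linked to sizing.

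The scale also matters. The ±0.63 is in SDs of the change score. In raw-score SDs, with an assumed pre-post correlation of 0.7, the half-width near d = 0 is 0.62 × √(2 × 0.3) = 0.48; at a correlation of 0.5 it is 0.62. The article gives no correlation.

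**Conclusion.** The sufficiency claim in Study samples is wrong as written and should be changed. The firm part is the precision: about ±0.63 SD of the change score with 20 analysed per arm, and wider with any loss of data. How often that would lead to a badly sized RCT rests on an assumed true effect. On the factor-of-two or wrong-sign measure it falls from about three-quarters of pilots at d = 0.3 to about a quarter at d = 1.0, so the frequency should always be quoted with its assumed effect. The size of 40 is not itself the fault: it supports a useful estimate of the SD and a preliminary estimate of the arm difference. This is a point the sponsor should act on, but it does not threaten the conduct of the pilot.

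**What to change.** 1. In Study samples, replace the sufficiency sentence. Say that the pilot will estimate the NHPT SD, with its confidence interval, and will report the between-arm difference with a 95% confidence interval as a preliminary estimate.
2. Add that the larger RCT will be sized on a justified, clinically important between-arm NHPT difference, with the pilot SD and an allowance for its uncertainty, and not on the observed pilot effect size. State whether the 32.8 seconds in the Data analysis plan is meant to serve as that between-arm target.
3. In Data collection, bring the wording on testing effectiveness into line with the planning aim stated in the abstract, the Background and the closing Discussion.

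The cost is a change of text. No extra patients or assessments are needed. The claim made for the pilot becomes more modest.

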### Data analysis plan

All data will be inputted in IBM SPSS statistics software, version 21 (Armonk, NY, USA). Descriptive statistics for the study population and outcome measures will be computed for both groups to verify that groups are similar preintervention. A repeated measures analysis of variance (ANOVA) will be used to compare the NHPT scores within and between groups; with repeated measures for time (pre intervention versus post intervention) between the groups (Rehab-let versus GRASP) and for interaction effect between time and group. A difference above 32.8 seconds [31] on the NHPT for the weaker upper extremity will be considered to be a clinically meaningful change. Differences in the upper extremity secondary measures as well as adherence (self-training time) and satisfaction will be compared as well. Intention-to-treat analysis will be conducted with the last observation carried forward method.

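### The primary NHPT analysis lists time, group and interaction effects without naming the treatment test; a baseline-adjusted between-arm difference would settle this and is usually more precise

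*Protocol article*

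**What the plan says.** Under Outcome measures, the protocol article states: "The primary outcome measure is improved dexterity, which will be assessed by The Nine Hole Peg Test (NHPT"). The Data analysis plan then fixes the model: "A repeated measures analysis of variance (ANOVA) will be used to compare the NHPT scores within and between groups". It specifies the effects as "with repeated measures for time (pre intervention versus post intervention) between the groups (Rehab-let versus GRASP") and "for interaction effect between time and group". None of the three is named as the treatment test, and no baseline-adjusted model is given.

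The hypothesis at the end of the Background is comparative: Rehab-let "will result in improved dexterity, increased self-training time and high satisfaction in individuals with stroke as compared to the control group".

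The baseline score exists and precedes allocation. Data collection says "The clinical measures mentioned above will be administered pre and post the intervention to test the effectiveness of the intervention", and Implementation of the intervention says "Following the first assessment, individuals will be randomly allocated to receive self-training either by Rehab-let (experimental group) or GRASP (control group"). The Data analysis plan also calls for descriptive statistics by group "to verify that groups are similar preintervention".

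Study samples gives 20 participants per arm and says the results will supply the effect size for powering a larger trial. The article gives no SD, pre-post correlation, alpha or power.

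**The concern.** A two-by-two repeated-measures ANOVA produces three F-tests that answer three different questions, and only one of them answers the trial's. In subacute in-patients who all receive standard care plus an active self-training programme, improvement over four weeks is likely in both arms whatever the apps do. A significant time effect therefore says nothing about Rehab-let against GRASP. The group main effect does compare the arms, but it dilutes the post-intervention difference with a baseline difference whose expectation is zero.

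Two things are at stake. The first is which number goes forward as the effect size for the next trial. If a halved difference were entered in a sample-size formula with the same SD, the required number would be 1/(1/2)² = 4 times too large. The second is precision: with 40 people and a baseline measure in hand, leaving that measure out as a covariate usually gives a wider interval than necessary.

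**Working it through.** The article states no power, alpha or variance, so there is no figure of its own to reproduce. The check compares the precision of the available contrasts.

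**Inputs.** n = 20 per arm and 1:1 allocation, with one pre and one post assessment and baseline before randomisation (all from the article). Assumed: equal pre and post SD (set to 1), pre-post correlation rho from 0.3 to 0.9, two-sided 5%, and for the power figures a post-intervention difference D = 0.8 SD.

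**What each effect estimates** (variance per person; multiply by 2/n for the contrast):

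- Interaction: the difference between arms in mean change. Expectation D, variance 2(1 − rho). With two time points this is exactly the t-test on change.
- Group main effect: the difference between arms in (pre + post)/2. Expectation (0 + D)/2 = D/2, variance (1 + 1 + 2·rho)/4 = (1 + rho)/2.
- Time: the mean change over both arms. It contains recovery common to both arms and is not a contrast between them.
- ANCOVA: the difference in post score adjusted for baseline. Expectation D, variance 1 − rho², multiplied by 1 + 1/(2n − 4) = 1 + 1/36 for estimating the slope.

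**Variance ratio, ANCOVA to interaction.** (1 − rho²)/[2(1 − rho)] = (1 + rho)/2 in large samples; at 20 per arm, (1 + rho)/2 × 37/36. Power is from the noncentral t (38 df; 37 for ANCOVA).

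| rho (assumed) | (1 + rho)/2 | × 37/36 | 40 people under ANCOVA equal, under interaction | Power %: interaction / group / ANCOVA |
|---|---|---|---|---|
| 0.3 | 0.650 | 0.668 | 60 | 54.9 / 33.4 / 72.2 |
| 0.5 | 0.750 | 0.771 | 52 | 69.3 / 29.6 / 80.1 |
| 0.7 | 0.850 | 0.874 | 46 | 88.9 / 26.7 / 92.5 |
| 0.8 | 0.900 | 0.925 | 43 | 97.4 / 25.5 / 98.2 |
| 0.9 | 0.950 | 0.976 | 41 | 100.0 / 24.4 / 100.0 |

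Break-even: (1 + rho)/2 × 37/36 = 1 gives rho = 72/37 − 1 = 0.946. Above that, ANCOVA gains nothing at this size.

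In terms of interval width, √0.771 = 0.88 and √0.874 = 0.93, so the interval is about 12% narrower at rho 0.5 and 7% narrower at rho 0.7.

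**Simulation check** (20,000 trials per setting, rho 0.5, 0.7 and 0.9). The variance ratios were 0.77–0.78, 0.87–0.88 and 0.97–0.98, in agreement with the table. ANCOVA type I error was 4.8–5.0%. With no treatment difference and an assumed 0.8 SD recovery common to both arms, the time effect was significant in more than 99% of trials.

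**Chance imbalance.** The baseline difference between arms has SD √(2/20) = 0.316 SD. Given an observed difference d, the expected change-score contrast moves by −(1 − rho)·d. A one-SD imbalance (0.316) therefore shifts it by 0.5 × 0.316 = 0.16 SD at rho 0.5 and 0.3 × 0.316 = 0.09 SD at rho 0.7. ANCOVA conditions on d and removes this shift.

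**The case against.** The strongest reply is that the plan already contains a valid between-arm test. The interaction is listed, is unbiased under randomisation and holds its error rate. The context points to it as well: the outcome is worded as improvement, the hypothesis is relative to control, and the clinical threshold is a change. That stands. A reader might infer that the plan has no valid treatment test, and the article does not support this. What it lacks is the designation.

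A reader might also infer an inflated error rate. If either the group or the interaction effect could count as success, type I error would be 1 − 0.95² = 9.75%. The article announces no such rule and sets no alpha, so this is a risk left open by the wording and not a property of the plan.

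A third tempting reading is that the baseline comparison steers the analysis. It is descriptive; no significance test and no analysis decision is attached to it. A fourth is that change scores are biased by regression to the mean. Over randomisations they are not; the shift shown above holds only conditional on an observed imbalance.

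The efficiency gain is also conditional. The article gives no correlation, and the same test on the same hand four weeks apart could correlate highly, in which case the gain is about 7% of variance at 0.8 and 2% at 0.9. Carrying the last observation forward with a single post assessment sets post equal to baseline for dropouts, which tends to raise the analysed correlation and shrink the gain further. Finally, this is a pilot with no claimed power, so the 0.8 SD power figures are illustrative. These points limit the size of the gain. They do not supply the missing designation, which matters at every correlation and bears directly on the pilot's purpose of supplying an effect size.

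**Conclusion.** The point holds as one of designation and precision, not validity. The article fixes a primary model with three effects and does not name the one that tests Rehab-let against GRASP. The interaction does so validly; the group effect estimates half the treatment effect, and the time effect is not a treatment comparison. Adjusting for baseline NHPT would reduce the variance of the treatment contrast by about 33%, 23%, 13%, 7.5% and 2% at correlations of 0.3, 0.5, 0.7, 0.8 and 0.9, with nothing to gain above about 0.95.

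These sizes rest on equal pre and post SDs, 20 analysed per arm and an assumed correlation. The finding about designation rests on none of these. It is a worthwhile improvement and not the repair of a broken analysis. It concerns the NHPT only, since the article fixes no model for the secondary measures.

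**What to change.** In the Data analysis plan, name one primary contrast: the between-arm difference in post-intervention NHPT, adjusted for baseline NHPT by ANCOVA, reported with its 95% CI. State that this estimate is the effect size to be used in planning the later trial. Report the time effect, within-arm changes and the baseline table as description only. If the repeated-measures model is kept, the least that is needed is a sentence naming the interaction as the sole treatment test; that settles the ambiguity but gives up the gain in precision.

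The cost is a change of wording. It needs no new data, visits or software, and the article reports that recruitment is still under way, so the change can be made and dated before analysis.

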### Privacy, safety, and ethics

We have no safety or ethical concerns regarding this trial. Individuals will consent prior to enrollment. We already have an approval (#0125-13-SMC) from the Sheba Medical Center Institutional Helsinki Committee. Individuals will be encouraged to report adverse effects such as pain and, when necessary, the study will be stopped. Participants from both self-training interventions may potentially improve their dexterity and, therefore, benefit from the program.

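### With only a pre and a post assessment, LOCF gives every participant without a post NHPT exactly zero change, which can shrink, create or mask an arm difference depending on dropout

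*Protocol article*

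**What the plan says.** The Trial design section describes "A pilot single-blind randomized controlled study with assessments pre and post the intervention". The Blinding section confirms it: "Assessments pre and post the 4-week self-training intervention will be administered by assessors blinded to the group allocation". Table 2 lists the weekly therapist contacts apart from the assessments: "Four meetings with the occupational therapist will be held during this time as well as pre and post assessment sessions". No interim NHPT is described.

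The primary analysis is a repeated-measures ANOVA of NHPT scores, "with repeated measures for time (pre intervention versus post intervention) between the groups (Rehab-let versus GRASP) and for interaction effect between time and group". The Data analysis plan then adds: "Differences in the upper extremity secondary measures as well as adherence (self-training time) and satisfaction will be compared as well". The next sentence is the missing-data rule, "Intention-to-treat analysis will be conducted with the last observation carried forward method", with no outcome exempted and no sensitivity analysis named.

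On expected change, the Privacy, safety, and ethics section says: "Participants from both self-training interventions may potentially improve their dexterity and, therefore, benefit from the program". Both arms also receive standard rehabilitation care (Trial design). The Study samples section intends the results to supply the effect size for powering a larger trial.

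**The concern.** LOCF needs a post-baseline value to carry. Here there is none, so the rule is baseline carried forward under another name. Participants are subacute inpatients, eligible from 1 week after stroke, who receive standard rehabilitation plus self-training in either arm. The rule assigns no recovery to each of them who lacks a post NHPT, which conflicts with what the article itself expects.

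Two things are at stake. The time-by-group comparison of NHPT can be distorted, and the pilot's main product, an effect size for the next trial, carries the same distortion. There is also a question of scope: the LOCF sentence directly follows the one naming self-training time and satisfaction, and the rule does not suit either.

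**Working it through.** **Figures in the article.** It gives no power calculation, SD, expected change or dropout rate, so there is no planning figure on this point to reproduce. The sample size is 20 + 20 = 40.

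**Step 1: what LOCF does.** With one pre and one post value, a missing post value is set equal to the pre value, so the change is 0. With two times and two groups, the time-by-group interaction is the same test as a t-test on change, so these zeros enter the primary test directly.

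**Step 2: expected arm difference.** Let c be the mean improvement (reduction in NHPT time) in the control arm, D the true extra improvement with Rehab-let, and pE and pC the dropout proportions in the Rehab-let and control arms. If dropout is unrelated to outcome:

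- LOCF difference = (1 − pE)(c + D) − (1 − pC)c
- Bias = pC·c − pE(c + D)

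With pE = pC = p the LOCF difference is (1 − p)D. It is therefore unbiased when D = 0 and shrunk by the fraction p otherwise.

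**Step 3: illustration.** The assumptions below are not in the documents: c = 25 s; SD 25 s at each time; pre-post correlation 0.7; 20 per arm; each participant drops out at random with the stated probability. Rejection rates are simulated, two-sided 5%.

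| D | Dropout, Rehab-let v control | LOCF difference | LOCF rejection rate |
|---|---|---|---|
| 0 | 20% v 20% | 0.8×25 − 0.8×25 = 0 s | about 5% |
| 0 | 10% v 20% | 0.9×25 − 0.8×25 = 2.5 s | about 7% |
| 0 | 10% v 30% | 0.9×25 − 0.7×25 = 5 s | 12–13% |
| 15 s | 20% v 20% | 0.8×40 − 0.8×25 = 12 s | about 39% |
| 15 s | 30% v 10% | 0.7×40 − 0.9×25 = 5.5 s | about 12% |

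In the 15 s, 20% v 20% row, the same change-score test on observed data estimates 15 s with power of about 56%, and a baseline-adjusted analysis reaches about 61%. So 56 − 39 = 17 points are due to LOCF, and the further 5 to baseline adjustment.

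**Step 4: the exported effect size.** In that same row:

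- The SD of change without LOCF is 25 × √(2 × 0.3) = 19.4 s, so the standardised effect is 15/19.4 = 0.77.
- Under LOCF the variance in an arm with mean improvement m is 0.8 × 375 + 0.2 × 0.8 × m². This is 400 for m = 25 and 556 for m = 40, giving a pooled SD of √478 = 21.9 s.
- The standardised effect under LOCF is 12/21.9 = 0.55.
- Required sample size varies with the inverse square, so the next trial would be planned about (0.77/0.55)² ≈ 2 times as large.

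**Step 5: a second set of assumptions.** This takes the article's 32.8 s clinically meaningful change as the scale, with SD of change from 16.4 to 49.2 s and fixed numbers of dropouts.

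- Both arms improve 32.8 s, dropout 2 v 6 of 20: false difference 0.9×32.8 − 0.7×32.8 = 6.56 s, type I error 6.7% to 11.6%.
- Both arms improve 32.8 s, dropout 4 v 4: no bias, and a conservative test (0.7% to 3.8%).
- True difference 32.8 s (65.6 v 32.8), dropout 4 v 4: estimate 26.24 s, a 20% loss. At SD 32.8 s, power falls from 78% to 64%.

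**The case against.** The strongest reply is that the bias is conditional, and this stands. With equal dropout and no true effect the difference is unbiased, and the 12–13% error rate needs a threefold imbalance in dropout. This is also a 40-person pilot: under the Step 3 assumptions the standard error of the arm difference with no dropout is 19.4 × √(2/20) = 6.1 s, larger than the 5 s spurious effect. The estimate will be imprecise whatever the method. That does not justify adding an avoidable systematic error to a figure meant for planning.

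Several stronger readings are tempting but not supported:

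- **That the rule favours Rehab-let.** The article hypothesises more training time with Rehab-let, which is not the same as better attendance at the post assessment. With a true benefit and equal dropout, LOCF works against Rehab-let.
- **That fast recoverers will be missing because they go home early.** Table 2 says "Intervention will take place in in-patient rehabilitation departments", but nothing says that discharged participants miss the post assessment. If they did, dropout would depend on outcome. An analysis under missing at random would then be biased too, and with no interim NHPT a mixed model could not recover the lost information.
- **That LOCF credits training never done.** A participant who stopped after five 60-minute sessions would have 300 min recorded as 1,200 min (20 × 60) only if the last daily entry were copied into every later session. The article says only that training time comes from daily logs. A sum of logged minutes adds nothing after stopping.

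**Conclusion.** The rule is wrong as written for the primary outcome. That every participant without a post NHPT receives zero change follows from the article alone, as does the conflict with the improvement it expects in both arms.

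The effect on the result is conditional on dropout, which the article does not state. If dropout is unrelated to outcome, a true effect shrinks by the dropout fraction when dropout is equal. When dropout differs between arms, the rule can create or mask a difference of several seconds. The seconds, error rates and power figures rest on the assumed recovery, SD, correlation and dropout.

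For self-training time and satisfaction the finding is only that the scope of LOCF needs stating. Satisfaction with the programme, asked after training, has no earlier value to carry.

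**What to change.** Replace LOCF as the main method in the Data analysis plan:

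- **Main NHPT analysis.** Baseline-adjusted ANCOVA, or a likelihood-based model of all available NHPT data, by allocated arm and under missing at random.
- **Sensitivity analyses.** Keep baseline carried forward here only. Add an analysis under missing not at random, for example multiple imputation with arm-specific shifts in the imputed post values, because loss may depend on recovery.
- **Scope.** State that LOCF does not apply to self-training time, which is the sum of minutes actually logged with none credited after stopping. State that satisfaction is analysed on observed responses.
- **Reporting.** Give the number without a post NHPT and the reasons, by arm, next to any effect size passed to the larger trial.

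The cost is one paragraph of text and standard methods. The downside is that the main analysis relies on missing at random, and participants without a post value are either left out (ANCOVA) or represented through the model. Hence the sensitivity analyses.
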